### Secondary endpoints

#### Tissue collection and reports

The aim is that at least in 85% of all patients included tumour and blood collection will be successful. Feasibility of routine WGS analysis in this patient population will be measured by the percentage of patients for whom a successful WGS report can be generated. The aim is that at least 80% of the patients for which tumour and blood material was collected will receive a WGS report. Reasons for not being able to produce a patient report based on WGS include low or no tumour cellularity of the available tumour material (expected 15 to 20% based on previous experiences), low DNA yield or quality (e.g. due to necrosis, < 3%), and technical failures (< 2%).

#### Targeted treatment options

Another important endpoint is the added value of WGS indicated by the number of targeted treatment options identified. As mentioned before, actionability is based on information in public knowledge bases and can be split by ESCAT classification evidence levels [22]. Because the ESCAT levels are not yet available in public knowledge bases, Food and Drug Administration (FDA) approved drugs and drugs for which a trial is currently available, bases on the JAX CKB clinical knowledgebase, will be reported by Hartwig. Interpretation of the genomic variants in terms of pathogenicity and actionability will be done by using criteria for classifying pathogenic variants [26] and expert interpretation in molecular tumour boards.

The expectation is that at least one potentially actionable DNA alteration should be identified in at least 75% of the patients with a WGS report. Consequently, the number of experimental treatments available for these patients with a recurrent GBM will be measured. At least 50% of the identified indications should be available (albeit off-label drugs) through a study, including the DRUP study. A third endpoint regarding targeted treatment options is a doubling of the number of patients starting a targeted treatment in presence of one or more actionable variants (i.e. from 16 to 32%). We aim to dissect this increase for improvements due to diagnostics and/or availability of novel drugs by both comparing historic diagnostic yields as well as treatments given and outcomes.

#### Progression free survival

Finally, data about the median progression free survival after reresection will be collected by calculating the time between the date of the reresection and the date of clinical and/or radiological progression. The aim of the GLOW study is to improve the median progression free survival by at least three months for the patients who are treated based on WGS results compared to patients in the historical cohort who are not treated based on WGS results.

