## Background

Glioblastoma (GBM), the most common glial primary brain tumour, is almost always lethal. In the Netherlands, every year approximately 600 patients are diagnosed with this heterogeneous disease. Standard treatment for patients with newly diagnosed GBM consists of maximal safe surgical resection followed by postoperative radiation with concomitant and adjuvant temozolomide therapy [1]. Despite this intensive treatment scheme, these tumours inevitably recur and the prognosis of patients remains poor with a median survival of 14 months [2]. At the time of recurrence, only a small number of patients with well-localized tumours are eligible for re-resection. Systemic treatment is commonly suggested for recurrence, of which nitrosoureas or retreatment with temozolomide being mostly used with limited progression-free survival rates at 6 months (15–20%) and objective response rate of less than 10% [3–7]. Patients with an O6-methylguanine DNA methyltransferase (MGMT) promoter-methylated recurrent tumour may benefit from a temozolomide rechallenge, from lomustine or even the combination of both [8–10]. Outside of the European Union, bevacizumab has been approved for relapsed GBM [11, 12]. Some patients with relapsed GBM undergo re-irradiation, which may result in local disease control in a proportion of patients [13–17]. However, this is not always feasible due to the hazards of cumulative (cognitive) neurotoxicity.

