Unfortunately, the results of dedicated trials with new drugs have been very disappointing. Target pre-screening, if applicable, was usually performed on archival tumour material, limited gene panels were used and not in every case a central review was performed. Targeted treatment options are becoming increasingly available for cancer patients, however studies on molecular targets for recurrent GBM patients have not yet led to clinical advantages [18]. Still, there is a major unmet need for this patient category as demonstrated by the limited treatment options and very poor survival. Furthermore, the organisation of standard-of-care (SOC) molecular testing for GBM is suboptimal. First, molecular tests are currently performed sequentially, which takes more time, especially in absence of gene panels. Second, because of this organization, tissue might become scarce. Third, different centers use different molecular panels, which are not all tailored towards identifying relevant biomarkers for (experimental) targeted treatments. Whole genome sequencing (WGS) will provide all molecular information in a single test and within a limited time of ten to fourteen days. Furthermore, additional stratification biomarkers for treatments can be identified using WGS. Although WGS is validated as a clinical diagnostic test [19, 20], its implementation in routine care environments is still slowly growing, although in the Netherlands, the non-profit organisation Hartwig provides access to WGS-based testing to all hospitals. The potential of WGS in the area of personalised medicine for patients with cancer has been demonstrated before, but it has never been prospectively studied as a SOC procedure in patients with a recurrent GBM [20, 21].

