## Objectives

### Primary objective

The primary objective of the GLOW study is to determine the percentage of patients who receive targeted therapy after surgery, including experimental therapy based on the WGS report, which should ultimately result in more effective treatment (not part of the study) and improved survival, which will be measured as overall survival (OS) within GLOW.

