### Treatment decision

The WGS report that will be made available by Hartwig (see Additional file 1 for an example) will be sent to the local pathologist and local study coordinator, who will add the report to the electronic patient files and enters relevant information to a nationwide network and registry of histo- and cytopathology in The Netherlands (PALGA) [23]. In addition, patient reports will be returned to the treating medical specialist as well as to central and local principal investigators. The neuro-oncology team will discuss the results and allocate subsequent treatment accordingly. If needed, the local neuro-oncologist can consult a centralized molecular tumour board which will also receive the anonymised report for central data management. In case of a persistent discordance between the results of WGS and SOC diagnostics, the SOC findings will be leading in the treatment decision. Such discrepancies will be followed up with revalidation of the results (e.g. to exclude sample heterogeneity as a cause) including the use of an independent orthogonal assay when needed.

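### The PFS aim starts its clock at reresection but is judged only in patients later treated on WGS results, so two opposite biases enter and their net direction cannot be determined

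*Protocol article*

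**What the plan says.** In the protocol article, the section Progression free survival fixes four elements of this endpoint.

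- **Clock:** PFS is obtained by "calculating the time between the date of the reresection and the date of clinical and/or radiological progression".
- **Aim and analysed group:** to "improve the median progression free survival by at least three months for the patients who are treated based on WGS results".
- **Comparator:** "patients in the historical cohort who are not treated based on WGS results".
- **Measure:** the difference in median PFS.

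Secondary objectives repeats the three-month aim for the same treated group.

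On when WGS-based therapy begins, the article says little. Primary objective concerns "the percentage of patients who receive targeted therapy after surgery, including experimental therapy based on the WGS report". Treatment decision says that "The neuro-oncology team will discuss the results and allocate subsequent treatment accordingly". Background gives the test turnaround as "within a limited time of ten to fourteen days". No section sets a window for starting therapy, or says whether it begins before or after a further progression.

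**The concern.** A group defined by something that happens after time zero cannot be compared from time zero with a group that carries no such condition. Two things go wrong, in opposite directions.

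1. **Late starters.** Suppose a patient progresses after reresection and only then starts WGS-based therapy. That patient counts as treated on WGS results, but the recorded PFS ended before the first dose. Such patients pull the treated-group median towards the control value.
2. **Guaranteed time.** A patient who starts WGS-based therapy before progression was progression-free up to that date by definition. Historical patients did not have to meet that condition. Such patients push the treated-group median up even if the therapy does nothing.

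At stake is how the PFS result is read. A gain of three months could arise partly from selection, and a shortfall could hide a real effect.

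**Working it through.** **The plan's own figures.** The only calculation in the article is the patient flow: 235 × 0.85 = 199.75, about 200 reresected, and 200 × 0.80 = 160 WGS reports. Both reproduce. No PFS assumption underlies them.

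**Size of the treated group.** Using the stated aims of 75% with an actionable alteration and 32% of those starting targeted treatment, 160 × 0.75 × 0.32 = 38.4, about 38 patients. That is 24% of those with a report (38.4/160) and 19% of those reresected (38.4/200).

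**Inputs that are assumed**

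- Control PFS is exponential. The rate comes from Background, which reports "limited progression-free survival rates at 6 months" of 15 to 20% for systemic treatment at recurrence. This is a proxy, not a figure for reresected patients.
- f is the share of WGS-treated patients who start after progression. The documents do not give it.
- d is the time from reresection to start of therapy, in months. The documents do not give it; the 10 to 14 days cover the WGS test only.

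**Control median.** m = 6 × ln 2 / (−ln PFS6). PFS6 = 0.15 gives m = 2.19 months and PFS6 = 0.20 gives m = 2.58. A 3-month gain means a median of 5.2 to 5.6 months, a hazard ratio of about 0.42 to 0.46.

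**(a) Late starters alone.** True gain is 3 months, late starters have control-like PFS, and guaranteed time is ignored. Solve f × 0.5^(t/m) + (1 − f) × 0.5^(t/(m+3)) = 0.5 for t; the observed gain is t − m.

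| f | Observed gain (months) |
|---|---|
| 10% | 2.55 to 2.57 |
| 20% | 2.13 to 2.16 |
| 30% | 1.75 to 1.78 |
| 50% | 1.09 to 1.13 |

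**(b) Guaranteed time alone.** f = 0 and no drug effect. The median becomes d + m, so the apparent gain is d: 0.5 month at d = 0.5, 1 at d = 1, 2 at d = 2.

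**(c) Both together.** A share f progressed before d. The rest are progression-free to d and then exponential. For f below 50% the median lies beyond d, which gives:

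- no drug effect: gain = d + m × log2(1 − f);
- true 3-month gain from start of therapy: gain = d + (m + 3) × log2(2(1 − f)) − m.

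| d | f | Gain, no drug effect | Gain, true +3 months |
|---|---|---|---|
| 0.5 | 10% | 0.11 to 0.17 | 2.65 to 2.71 |
| 0.5 | 20% | −0.33 to −0.21 | 1.70 to 1.83 |
| 1 | 10% | 0.61 to 0.67 | 3.15 to 3.21 |
| 1 | 20% | 0.17 to 0.29 | 2.20 to 2.33 |
| 2 | 10% | 1.61 to 1.67 | 4.15 to 4.21 |
| 2 | 20% | 1.17 to 1.29 | 3.20 to 3.33 |
| 2 | 30% | 0.67 to 0.87 | 2.13 to 2.33 |

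With the same true effect, the observed gain in this table runs from about 1.7 to 4.2 months, depending only on two quantities that the documents do not give.

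**The case against.** The strongest reply is that starts after progression are an inference. No section says they will occur. The article describes a short test turnaround, a more accurate stratification before treatment, and a report meant to help the treatment decision after reresection. All of this points to therapy before progression in many patients. The article also condenses a fuller protocol, which may set a start window. This stands: how often late starts occur is unknown. It does not remove the point, because a window that excluded late starters would leave the guaranteed-time bias in full (f = 0 in the working).

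A reader might infer more: that early progression is common, so that most treated patients start late and a real gain must be diluted below three months. The documents do not support that. The proxy rate describes how fast all patients progress, not the share of WGS-treated patients who start late; someone who progresses early and never receives WGS-based therapy is not in the analysed group. A long wait for therapy, which would make late starts more frequent, also lengthens the guaranteed time. At f = 10% and d = 1 or 2 months the observed gain exceeds three months.

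Two further points are fair. The proxy rate is weak for patients fit enough for reresection. The study also evaluates a diagnostic strategy, for which reresection is a sound common origin and delay in reaching therapy is part of the effect. The second point supports the fix: it justifies an all-patient comparison from reresection, not one restricted to those later treated.

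**Conclusion.** The point holds as a misalignment between the time origin and a treatment-defined group, with a bias of undetermined net direction. It is not established that the result will be diluted below target, nor that it will be inflated.

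The mismatch is in what the article states, not in a detail left to another document: clock, group, comparator and target are all given, and they do not fit together. Each mechanism is of a size that matters against a 3-month aim. Late starts alone reduce a true 3-month gain to about 2.1 to 2.2 months at f = 20%. Guaranteed time alone adds about d months with no effect. These sizes rest on exponential PFS, the proxy six-month rate, and assumed f and d. I also read the single progression date as the first progression after reresection, which the text does not spell out.

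The consequence is limited to a secondary aim. Meeting or missing it could not be attributed to WGS-based therapy. It should be corrected, but it does not undermine the study's feasibility results.

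**What to change.** 1. Assess the PFS aim by comparing all reresected GLOW patients with the historical cohort, both from reresection. Alternatively, use all patients with a WGS report, against a historical group defined in a matching way. This agrees with Study design, which compares the prospective cohort's outcomes with the historical cohort's. Change Secondary objectives to match.
2. Record the start date of WGS-based therapy and its position relative to progression.
3. Report PFS in WGS-treated patients descriptively, split by start before or after progression.
4. If a treated-patient comparison is kept, use a landmark analysis or treat therapy as a time-dependent covariate. Do not simply drop patients who started after progression: that leaves only patients known to be progression-free at the start of therapy and gives the guaranteed-time bias free rein.

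**Cost.** Wording and one additional date. Treated-patient PFS becomes descriptive, in about 38 patients split in two. The all-patient difference will also be much smaller. If 24% of patients with a report gain 3 months and 76% gain nothing, the formula in (a) with f = 0.76 gives a difference in medians of about 0.4 to 0.5 month. The 3-month target therefore cannot be carried over unchanged and has to be restated for the all-patient comparison.

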## Discussion

The GLOW study is a unique trial since it is the first time that patients with a recurrent glioblastoma will prospectively obtain a standard-WGS analysis to identify targeted treatment options that could help treatment decision after reresection. The prognosis in this patient population remains very poor, and several questions about the best treatment strategy at the time of first recurrence of the tumour are still unanswered. This study aims to generate evidence for the added value of WGS as a routine diagnostic in this patient population. If a significant benefit is demonstrated, this will show cost effectiveness. However, it is important to be aware of the limitations of this study.

From a patient’s perspective, it can be essential to know everything is done to give them an opportunity of a targeted treatment, whether experimental or not. Notwithstanding, it is crucial to remember that the GLOW study will not investigate the treatments itself, but focusses on the clinical effect of a different diagnostic strategy. We do fully realise that with today’s knowledge and available drugs, this study may not reach successful endpoints due to limited effectiveness of the mostly experimental treatments that will be given based on WGS. Secondary endpoints, as the feasibility of routine WGS diagnostics, are therefore also important for determining next steps as the future targeted drug portfolio is likely to be expanded significantly [27, 28]. Another potential limitation could be the situation in which an actionable target is found in absence of a recruiting drug study. However, previous studies on WGS-based diagnostics in cancer, i.e. the beforementioned CPCT-02 and WIDE studies, do not support this potential objection. Moreover, experimental targets will not be reported to avoid these situations. At the same time, a close monitoring of the expanded use of existing anticancer drugs could lead to new treatments [29]. Finally, the heterogeneity of glioblastoma, tumour penetrating issues and pathway redundancy are all limitations that could hamper successful targeted treatments and should therefore be kept in mind when analysing the results of this study.

In conclusion, the GLOW study aims to investigate the feasibility, validity, utility and value of WGS for recurrent GBM patients. This will allow for disclosure of potentially novel targets for therapy for these patients.

## Data Availability

The datasets obtained during the current study, data management procedures or the full protocol will be available from the corresponding author upon reasonable request. Genomics data and certain clinical data of patients that have given consent for re-use of their data are made readily available through the standard controlled access mechanism of the Hartwig Medical Foundation (see https://www.hartwigmedicalfoundation.nl/applying-for-data/ for details and application forms).
